### Statistic analysis

Statistical analyses will be under the responsibility of Lyon CM2R (Research and Resources Centre Memory).

#### Population descriptive analysis

Descriptive analysis of data collected from patients will be conducted. Quantitative variables will be described according to their size, mean, standard deviation, median, quartiles, and range of values. Qualitative variables will be described by numbers and percentages.

#### Principal objective: Analysis of predictive markers

An analysis of predictors of occurrence of loss of autonomy at 2 years will be conducted on patients with dementia, by providing for qualitative factors, the distribution of patients with loss of autonomy and quantitative factors, means ± standard deviation. The predictive markers will be the clinical, radiological and biological measures.

Correlations analysis will be used to compare the Pearson correlation coefficient between the DAD and markers.

Analysis of variance and covariance will be used to compare means of continuous variables, including baseline scores and changes in scores over time. In multivariate analysis based on a mixed regression model will then estimate the change in score slope of the Inclusion to 2 years and the adjusted effects of predictive markers (imaging and biomarkers).

#### Secondary objectives

The following analyses will be used to assess secondary objectives: Correlations by Pearson’s correlation coefficient, Multivariate analysis: mixed regression model, Wilcoxon signed rank test, Logistic regression models and Percentages per group will be compared by Pearson’s Chi2 test (if the numbers are expected greater than or equal to 5), otherwise by Fisher’s exact test.

#### Statistical significance level

Test results will be defined as statistically significant at *p* < 0.05.

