**Discussion:**

This study aims at identifying the best combination of markers (clinical, neuropsychological, MRI, SPECT-DaTscan®, PET and CSF) to predict disability progression in elderly patients presenting coexisting patterns.

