## Methods and design

### Study aims

#### Principal objective

To identify imaging markers illustrating co-lesions of Alzheimer’s, cerebrovascular and Lewy body types of dementia the most predictive of functional disability progression.

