#### MRI: Parameters studied and sequences

This acquisition is included in the clinical usual practice and will be performed on 3 T MRI in all centres.

A morphologic MRI will be performed as part of the battery of exploratory tests habitually carried out when a patient presents with degenerative cognitive disorders on diagnosis.

Parameters studied will be brain volume, ventricular volume, regional cortical volume, hippocampal volume, ischemic vascular lesions and microbleeds.

These analyses will perform on:1 mm isotropic 3D T1 sequences without contrast injection for the quantification of Brain Parenchymal Fraction and VentriclesT2 gradient echo sequence, for the detection of microbleeds and amyloid angiopathy1 mm isotropic 3D FLAIR sequence (only for 3 T) or 3 mm axial 2DFLAIR (1.5 T), for the quantification of vascular and bright objectsDiffusion (b = 1000) with ADC cartography, for silent infarcts

Processing of MRI data will be performed by the “Centre d’Acquisition et de Traitement Automatisé des Images” (CATI, Head: [name], Orsay). Quality control at the different steps of MRI data acquisition will be made.

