### Sample size

The Required number of subjects is estimated on the primary endpoint: disability progression at 2 years. From the following hypothesis:Frequency of disability progression at 2 years = 40%Relative risk of rapid disability progression at 2 years related to global atrophy = 1.6Alpha risk (α) = 5%Statistical power (1- β) = 90%Two-tailed test

The Required number of subjects is 178. With an expected drop-out rate of 20%, the number of subjects to be included is estimated at 214 patients.

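### A flat 5% level covers a search over many markers, although the sample size rests on one test of one marker, and the planned association measures do not show how well a marker combination predicts

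*Protocol article*

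**What the plan says.** All references are to the protocol article.

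- *Statistical significance level* is one sentence: "Test results will be defined as statistically significant at" p < 0.05. It draws no distinction by marker, method or outcome.
- *Sample size* assumes "Frequency of disability progression at 2 years = 40"%, a relative risk of 1.6 for one marker (global atrophy), alpha 5%, "Statistical power (1- β) = 90"% and a "Two-tailed test". It arrives at 178 patients, raised to 214 for drop-out.
- *Principal objective* (study aims) seeks imaging markers, in the plural, that are "the most predictive of functional disability progression". The abstract's discussion speaks of "identifying the best combination of markers".
- *MRI: Parameters studied and sequences* lists six classes: "Parameters studied will be brain volume, ventricular volume, regional cortical volume, hippocampal volume, ischemic vascular lesions and microbleeds". The SPECT and amyloid PET sections add two modalities.
- *Principal objective: Analysis of predictive markers* takes clinical, radiological and biological measures as candidates. It plans descriptive comparisons, Pearson correlations with the DAD, analysis of variance and covariance, and a mixed regression model with adjusted marker effects. Global atrophy is not singled out there.

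**The concern.** The 5% in the sample size and the 5% in the analysis do not describe the same thing. In the first it is the error rate of one contrast on one marker. In the second it applies separately to every marker tested, and eight or more imaging markers are candidates before any clinical or biological measure is counted. Followed as written, the plan has an error rate across the imaging markers well above 5%, and nothing in the analysis section marks the powered test as different from the rest.

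The second part concerns the target. The aim is stated in terms of prediction and of a combination of markers. A correlation, a difference in group means or an adjusted coefficient describes association in the sample that produced it. None of them says how well a set of markers would predict progression in other patients, or how much one modality adds to another. At stake are the reliability of the list of imaging markers reported and whether the principal question is answered on its own terms.

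**Working it through.** **1. The plan's own figure.** Inputs from *Sample size*: 0.40, relative risk 1.6, two-sided alpha 0.05, power 0.90. Two readings are assumed: 0.40 is the rate in patients without atrophy, and the two groups are equal in size.

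- p1 = 0.40; p2 = 0.40 × 1.6 = 0.64; difference 0.24; mean 0.52.
- n per group = [1.960 × √(2 × 0.52 × 0.48) + 1.282 × √(0.40 × 0.60 + 0.64 × 0.36)]² / 0.24²
- = [1.960 × 0.7065 + 1.282 × 0.6859]² / 0.0576 = 2.264² / 0.0576 ≈ 89.
- Total 178, as stated. (178 × 1.2 = 213.6, giving the stated 214.)

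The 178 is therefore exactly the size for one comparison on one marker at 5%.

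**2. Error across imaging markers at 0.05 each.** The article gives no test count. Assumed: six MRI classes + one DaTscan measure + one amyloid PET measure = 8, tested separately, none truly related to progression.

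If independent, P(at least one p < 0.05) = 1 − 0.95^k:

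| k | Chance |
|---|---|
| 6 (MRI only) | 26.5% |
| 7 (without PET) | 30.2% |
| 8 | 33.7% |
| 10 | 40.1% |
| 20 | 64.2% |

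The rows beyond 8 show what happens if regional volumes are tested one by one.

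Independence is unlikely among volume measures. Simulating eight two-sided z-tests with a common correlation (assumed; 400,000 draws) gives:

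| Correlation | Chance (k = 8) |
|---|---|
| 0.2 | 31.9% |
| 0.3 | 30.0% |
| 0.5 | 25.1% |
| 0.7 | 19.2% |
| 0.9 | 11.8% |

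Every value exceeds 5%.

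**3. What strict control over all eight would cost.** Bonferroni: 0.05 / 8 = 0.00625 per test, two-sided critical value 2.734. For 0.40 vs 0.64 with 89 per group:

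- (0.24 × √89 − 2.734 × 0.7065) / 0.6859 = (2.264 − 1.932) / 0.6859 = 0.48, so power is about 69% instead of 90%.
- Restoring 90% power would need 276 evaluable patients.

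**4. In-sample measures and ranking.** Two illustrations, both on assumed values.

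- *Apparent fit.* In an ordinary regression of k unrelated predictors on n patients, the expected R-squared is k / (n − 1). For 8 markers and 178 patients this is 8 / 177 = 0.045; for 15 markers, 15 / 177 = 0.085. The plan's joint model is a mixed model, so this shows the direction of the bias and is not a forecast.
- *Ordering by raw correlation.* With 178 patients, one marker at a true correlation of 0.30 and seven at 0.20 (sampling errors taken as independent), the best marker comes first in about 52% of samples. If the seven are at 0.25, it comes first in about 30%.

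**The case against.** **The article condenses a longer document.** Multiplicity handling, ranking criteria and internal validation are often left to a full protocol or analysis plan, and silence on them would be no finding. That stands for the detail. But the article is not silent on the significance level. It states one undifferentiated rule beside a sample size built on a single test, and an analysis plan that controlled error would have to depart from that published rule. The article also names the measures it will use for the principal objective, and these measure association.

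**The size is an upper value for an assumed count.** This stands. The 34% needs eight tests, all independent and all null. The plan's own premise of a relative risk of 1.6 for atrophy sits badly with a global null, and the rates apply to separate tests, not to the single joint model that is also planned. Hence the range in place of one figure.

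**Adjustment in a marker-finding cohort is debatable.** This also stands, and it is why strict familywise control is not asked for. An exploratory label would be enough.

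**Stronger readings that a reader might infer, and that the article does not support:**

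- *That p < 0.05 is the rule for choosing the most predictive markers.* The significance section only defines when a test is called significant. The analysis section compares correlations and fits a joint model.
- *That the plan has no valid way to rank markers.* Correlations can be ordered, if crudely and in-sample. What is lacking is a measure of predictive performance for combinations.
- *That chance findings pass unchecked into a later score.* *Perspectives* foresees validating a predictive score on a larger cohort, which is a safeguard.

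**Conclusion.** The point holds in limited form. A flat 0.05 level is set for a search over many markers, while the sample size covers one two-sided 5% test of global atrophy. If eight imaging markers are tested separately and all are null, the chance of at least one nominally significant result is about 34% under independence and about 12% to 30% for correlations of 0.9 to 0.3. It rises if regional variables multiply. The count of eight, the common correlation and the global null are assumptions, because the article gives none of these.

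The analyses named for the principal objective do not measure the predictive performance of a combination, which is what the objective and the abstract ask for. This part is weaker than the first, since a fuller document could supply the criterion. It is worth correcting because the change uses data already being collected.

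**What to change.** 1. In the analysis section, name the global atrophy test used for the sample size as the one test at the unadjusted two-sided 0.05 level.
2. Report the other imaging markers with false-discovery-rate control, or label them exploratory. Label the secondary analyses exploratory.
3. Answer the question of which markers predict best with the R-squared (for DAD change) or AUC (for loss of autonomy as an event) of nested models, corrected for optimism by bootstrap or cross-validation. Rank markers or combinations by the increment, and give its uncertainty.

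The cost is wording, some computing and fewer markers reported as significant. No further patients or measurements are needed. Spreading alpha equally over eight markers would cut power for the planned contrast to about 69% at 178 patients, so the powered marker should keep its own alpha.

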## Discussion

The CLEM study aims at better understanding the factors underlying functional disability progression, cognitive decline and behavioural disorders in coexisting AD, CVD and LBD at mild or moderate dementia stages. Its main objective is to identify imaging markers illustrating co-lesions, the most predictive of functional disability progression.

Different combinations of biomarkers may be used in a **differential diagnosis** of neurodegenerative/vascular diseases depending on the degree of clinical relevance. First, imaging, primarily MRI, is used to eliminate a non-degenerative cause, including the different types of CVD. In this way, the International Society for Vascular Behavioral and Cognitive Disorders (VASCOG) proposed criteria for vascular cognitive disorders, in line with the DSM-5, to take into consideration the developments in other cognitive disorders such as AD [28]. Then, in order to objectify the distribution of atrophy suggestive of specific neurodegenerative disease, MRI will remain an essential tool. Thus, to distinguish AD and LBD, medial temporal lobe atrophy is mainly associated with AD diagnosis, with a good discriminatory power with LBD in pathologically confirmed cases [29]. For similar levels of dementia severity, LBD appears to have greater involvement of subcortical brain atrophy than AD [30]. Hippocampal atrophy can also be observed in VaD [31] and in frontotemporal lobar degeneration (FTLD) [32]. However, Laakso et al. found that hippocampal atrophy is significantly greater in VaD patients than in control subjects but less than in AD patients [33]. And, differently from AD, in FTLD, atrophy in the temporal lobes preferentially involves the anterior part of medial temporal lobe and the amygdala more than the hippocampus [34]. Moreover, there was evidence of a difference in trends of atrophy in the cingulate (more anterior in FTLD and more posterior in AD) [32]. Diffusion tensor MRI can also be helpful in differentiating FTLD from AD with greater damage especially in frontal white matter in FTLD [35]. However, white matter hyperintensities has been reported as similar in AD and LBD [36] while a greater number of microbleeds (MBs) was reported in LBD than in AD [37].

In addition to these brain MRI biomarkers, SPECT and PET are also of interest in the differential diagnosis between LBD and other aetiologies of dementia [38, 39]. For-example, SPECT-DatSCAN showed that presynaptic dopaminergic neurotransmission (Dopamine transporter, DAT) in substantia nigra and striatum is typically deficient in LBD whereas no deficit was observed in AD [40]. Moreover, approximately 50% of people with LBD also have amyloid accumulation visualized using amyloid PET, in a very similar distribution to that seen in AD, but to a lesser extent and with amyloid plaques more often diffuse rather than neuritic [41, 42]. Other brain imaging markers, such as 99mTc-HMPAO SPECT and FDG-PET modality also support corroborative signs of focal atrophy and can aid the differentiation of AD, FTLD, VaD, and LBD [43].

Since alterations in the CSF have been detected up to decades before the appearance of clinical symptoms in particular settings [44], the value of CSF analysis is also relevant in the differential diagnosis. In this way, CSF amyloid and tau biomarkers can for-example distinguish AD from VaD with a specificity of 80% [45], but CSF amyloid is not helpful in distinguishing between AD and LBD [46].

With increasing age biomarkers are less efficient for differential diagnosis of neurodegenerative disease, probably due to **co-existing lesions**. The etiological diagnosis is difficult when patients disclose symptoms suggestive of various diseases. Although many reviews have addressed diagnostic and therapeutic issues in pure AD, CVD and LBD, very few have focused on coexisting lesions. For example, LBD and AD are distinct disorders but they often coexist. Indeed, in LBD patients, the density of senile plaques may be similar to that observed in AD [47] and these cases are often regarded as ‘mixed’ cases of LBD with associated AD (LBD/AD). Armstrong et al. showed that the Abeta pathology of LBD/AD cases is different to that observed in patients with AD alone [48].

Regarding AD and CVD, some evidence from amyloid PET imaging suggests that increased vascular risk [49, 50] such as hypertension, diabetes, and smoking and CVD [51, 52] such as stroke, lacunar infarcts, CAA, microbleeds, and WM changes may accelerate amyloid production/aggregation/deposition and thus contribute to the pathology and symptomatology of AD [53]. One of the mechanisms linking CVD to AD is decreased cerebral blood flow, which modulates amyloid precursor protein cleavage enzymes leading to increased amyloid production [54]. Additionally, the association of the APOE4 genotype with an increased risk for both AD and CVD further suggests a potential link between CVD, and AD [55]. At the same level of cognitive impairment, AD patients with concomitant CVD were reported to be older and more severely demented, but have less severe AD pathology than patients without CVD [56]. A combination of AD and CVD is usually registered as a close third, moving up to first or second in rank in community-based studies of the oldest of old.

Since then, it seems important to establish consensus about diagnosis criteria for underlying lesions that contribute differently in the **progression of cognitive, behavioural and functional impairment** compared to pure pathology. Most of the studies report on functional, behavioural, and clinical abnormalities in patients with pure pathologies. For example, in AD subjects, autonomy loss correlates with frontal, temporal, and occipital structure atrophy [57]. In the LBD group, increased rates of cortical thinning in the frontal and parietal regions are significantly correlated with motor deterioration [58]. Other studies comparing functional ability between pure pathologies showed that VaD may be associated with a faster decline in physical functionality compared to AD [59]. Another study of 84 patients showed that LBD patients were more functionally impaired and had more motor and neuropsychiatric difficulties than patients with AD with similar cognitive scores [60].

But less is known regarding coexisting lesions in the assessment of the progression of cognitive, behavioural, and functional impairment. Yet, according to different studies, AD/LBD combination tends to induce greater cognitive and behavioural impairment than pure LBD [61, 62]. A progressive cognitive impairment occurring after the age of 70 is often related to mixed lesions of neurodegenerative and vascular origins. This complicates one of the crucial challenges for the future of therapeutic approaches in the elderly which is to target the main pathological process responsible for disability. Indeed, Schäufele et al. showed that, by controlling the degree of severity of dementia variables, only age and disability contributed to the prediction of mortality in patients with Alzheimer type, vascular or mixed dementia [63]. The longitudinal design using imaging, biological, and clinical biomarkers may give insight into helping to predict the precise role and weight of each brain lesion type in the disability progression in the co-existing pathologies and to develop preventive strategies to reduce the burden of disability related to these co-lesions.

### Limitations and strengths

The CLEM study may have some limitations. Firstly, recruitment may be difficult. Given the age of the patients, this is a dense protocol including several imaging techniques and clinical and biological assessments even if some are optional. Ideally, this study would have necessitated to follow-up the subjects for a long time but longitudinal studies of LBD for example are difficult owing to the higher mortality rates compared to AD [64].

Also, neuropathological correlates may be lacking, since discrepancies between pathological findings and clinical, as well as neuroimaging data are well known. Patient autopsy would be interesting to establish convergence evidence from imaging and biological diagnosis.

The present study also has strengths. Literature often assesses pure pathology but considers coexisting pathology only at the time of death. Moreover, to our knowledge, CLEM is the first study to follow during 2 years the disability of patients with presumed co-lesions as assessed with clinical, radiological and biological markers.

### Perspectives

It is crucial to better understand the predictors of the responses to current or future specific treatments in elderly patients affected by neurocognitive disorders. Since efficiency of disease modifying drugs has not been disclosed yet, and since side effects must be carefully considered, we aim to better define the population who would benefit from specific symptomatic or disease modifying drugs. These drugs will increasingly have to target the actual pathological processes responsible for functional decline in the medium term.

This program will allow further research on a larger cohort, in particular to validate a predictive score of functional disability risk in elderly presenting with progressive cognitive decline. A brain donor program will be developed and based on this cohort to further study the intimated neuropathological processes associated to dementia in the elderly at the terminal stage. This will also help in adapting non-drug therapeutic approaches and co-morbidity care, as well as the prevention of impairment of quality of life for the patients and their caregivers, risk of institutionalization, and costs of care.

## Abbreviations

AD: Alzheimer’s disease
ADAS-cog: Alzheimer’s Disease Assessment Scale-Cognitive Subscale
ADL: Activities of Daily Living
ANSM: Agence Nationale de Sécurité des Médicaments French Agency for the Safety of Health Products
ARWM: Age-Related White Matter Changes
BREF: Batterie Rapide d’Efficience Frontale
CAA: Cerebral Amyloid Angiopathy
CDR: Clinical Dementia Rating scale
CHU: Centre Hospitalier Universitaire
CMRR: Centre de Mémoire, de Ressources et de Recherche
CPP: Comité de Protection de Personnes (French Committee)
CRA: Clinical Research Associate
CRF: Case Report Form
CSF: Cerebro-Spinal fluid
CVD: CerebroVascular Disease
DAD: Disability Assessment for Dementia
DMS: Delayed Matched to Sample
DO: Denomination Objet
EDF: Echelle de Dysfonctionnement frontal
FCRT: Free and Cued Recall Test
FLAIR: Fluid Attenuated Inversion Recovery
IADL: Instrumental Activities of Daily Living
LBD: Lewy Body Dementia
LBD: Lewy Body Dementia
LP: Lumbar Puncture
MBs: Microbleeds
MCI: Mild Cognitive Impairment
MMSE: Mini-Mental State Examination
MRI: Magnetic Resonance Imaging
MTA: Medial Temporal Atrophy
NPI: NeuroPsychiatric Inventory
PET: Positron Emission Tomography
RL/RI 16: Rappel Libre/Rappel Indicé 16 mots
SAE: Side Adverse Event
SPECT: Single Photon Emission Computed Tomography
TMT: Trail Making Test
VaD: Vascular Dementia
VBM: Voxel Basel Morphometry
